**Methods:**

This study will randomize 598 patients in a 1:1 ratio between the standard arm (MF SABR) and the experimental arm (SF SABR). This trial is designed as two randomized controlled trials within one patient population for resource efficiency. The primary objective of the first randomization is to determine if SF SABR is non-inferior to MF SABR, with respect to healthcare provider (HCP)-reported grade 3-5 adverse events (AEs) that are related to SABR. Primary endpoint is toxicity while secondary endpoints include lesional control rate (LCR), and progression-free survival (PFS). The second randomization (BC Cancer sites only) will allocate participants to either complete quality of life (QoL) questionnaires only; or QoL questionnaires and a symptom-specific survey with symptom-guided HCP intervention. The primary objective of the second randomization is to determine if radiation-related symptom questionnaire-guided HCP intervention results in improved reported QoL as measured by the EuroQoL-5-dimensions-5levels (EQ-5D-5L) instrument. The primary endpoint is patient-reported QoL and secondary endpoints include: persistence/resolution of symptom reporting, QoL, intervention cost effectiveness, resource utilization, and overall survival.

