In a study by Basch et al., changes in QoL in patients receiving outpatient chemotherapy for advanced solid tumours were compared [13]. Patients were randomly assigned to complete symptom monitoring electronically, or received standard of care, and results in this systemic therapy population showed a greater improvement in QoL and OS from baseline to 6 months in the symptom monitoring arm. Our study will implement similar methodology in the radiotherapy setting. We will examine differences in patient-reported QoL in the second randomization, comparing change in EQ-5D-5L scores between those who complete questionnaires alone and those who complete questionnaires, a symptom-specific survey and receive HCP-guided intervention.

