## Methods

The objective of this trial is to assess if there is non-inferiority in terms of HCP-reported grade 3 or higher toxicities, lesional control rate (LCR), PFS, cost-effectiveness, and OS in patients with 1-5 oligometastatic or oligoprogressive lesions receiving SF SABR compared to patients receiving MF SABR. The trial will also assess if radiation-related symptom questionnaire-guided HCP intervention provides improvement in patient-reported QoL, compared to no HCP intervention in a subset of sites. The methods to be employed in this trial follow similar methodology used in our current SABR-COMET-3 trial [14].

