#### 2^nd^ randomization

The sample size is based on hypothesized QoL differences (mean difference of 5.7) between the intervention arms based on the landmark Basch et al. study, as well as the unpublished standard deviation of 15.6 for EQ-5D-5L scores from our ongoing SABR-COMET-3 study to capture expected standard deviation for our patient population [13, 14]. Group sample sizes of 125 and 125 will provide 80% power to detect a significant difference based on an alpha of 0.05. We will plan an analysis of Arm A and B after 250 patients.

The total sample size for this trial is 598 based on the primary objective of the first randomization.

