### Primary endpoints

The primary outcome for the first randomization is HCP-reported toxicity including grade 3-5 adverse events that are possibly, probably, or definitely related to SABR using CTCAE version 5.0. HCP-reported toxicity will be collected at study visits using the AE form. AEs will be compared at the per patient level at any time point post-treatment. Overall rate of AEs is calculated based on the greatest reported severity of SABR-related AEs over the course of the study for each patient. Differences in rates of grade 3 or higher toxicity between groups will be tested using the chi-square test or Fisher’s exact test, as appropriate. Non-inferiority will be assessed using the Farrington-Manning test.

Primary outcome for the 2^nd^ randomization is participant-reported QoL as measured by the EQ-5D-5L. Differences in participant-reported QoL between groups will also be tested using the chi-square test or Fisher’s exact test, as appropriate with non-inferiority assessed using the Farrington-Manning test.

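### The EQ-5D-5L primary endpoint of the second randomization is assigned tests for proportions and a non-inferiority test, although its objective and sample size call for superiority on a mean score

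*Protocol article*

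**What the plan says.** The question for Arms A and B is set out consistently in several places in the protocol article.

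- Abstract, Methods: the aim is to "determine if radiation-related symptom questionnaire-guided HCP intervention results in improved reported QoL".
- Methods, opening paragraph: the trial will assess whether the intervention "provides improvement in patient-reported QoL, compared to no HCP intervention in a subset of sites".
- Background: the second randomization is described as "comparing change in EQ-5D-5L scores between those who complete questionnaires alone" and those who also receive the symptom survey and the guided intervention.
- Sample size calculation, 2nd randomization: the size rests on "hypothesized QoL differences (mean difference of 5.7) between the intervention arms" and on an "unpublished standard deviation of 15.6 for EQ-5D-5L scores". It concludes: "Group sample sizes of 125 and 125 will provide 80% power", at alpha 0.05.
- DSMC and interim analyses: if the quality-of-life analysis at 250 patients is significant, the superior arm is chosen and all later patients are assigned to it.

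The analysis is set out in Statistical considerations, Primary endpoints. Its first paragraph gives toxicity a chi-square or Fisher's exact test, with non-inferiority by Farrington-Manning. Its second paragraph turns to the EQ-5D-5L: "Differences in participant-reported QoL between groups will also be tested using the chi-square test" or Fisher's exact test, again with non-inferiority by Farrington-Manning.

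**The concern.** Chi-square and Fisher's exact tests compare categories. Farrington-Manning compares two proportions against a margin. They suit the toxicity endpoint, which is a yes/no outcome per patient with a 5% margin. The EQ-5D-5L endpoint is described everywhere else as a numeric score, and the article gives neither a cut-off that would make it binary nor a margin for it. The word 'also' and the identical list of tests suggest that the toxicity paragraph was carried over.

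Two things are at stake. First, the power statement belongs to a comparison of means, so it does not describe the test that is named. Second, this is a primary endpoint whose result changes the conduct of the trial: an ill-fitting difference test would feed the decision to stop randomizing between Arms A and B. The added non-inferiority test, whatever its result, cannot show the improvement that the objective asks about.

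**Working it through.** **Inputs.** From Sample size calculation, 2nd randomization: difference 5.7, SD 15.6, 125 per arm, power 80%, alpha 0.05. Sidedness is not stated; two-sided is assumed. Allocation is 1:1.

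**Step 1: reproduce the stated size as a comparison of means.**

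- n per arm = 2 × (1.96 + 0.842)² × (15.6/5.7)² = 2 × 7.85 × 7.49 ≈ 117.6, so 118. The exact t-test gives 119.
- Power at 125 per arm: standard error = 15.6 × √(2/125) = 1.973; 5.7/1.973 = 2.889; Φ(2.889 − 1.960) = Φ(0.929) = 82.3%. The exact t-test gives 82.1%.
- A one-sided test would need 93 per arm and would have 89.3% power at 125, which does not fit.
- Exactly 125 results from a rank test (119 ÷ (3/π) = 124.6) or from a 5% dropout allowance (118 ÷ 0.95 = 124.2, rounded up). The article names neither.

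The stated 125 per arm for 80% power is therefore consistent with a two-sided comparison of numeric scores, and slightly conservative.

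**Step 2: power of the named test on the same effect.** No cut-off is given, so the score is dichotomised under an assumed model: normal scores, equal SD, and a shift of 5.7/15.6 = 0.365 SD. Chi-square power is Φ[(|p₂ − p₁| − 1.96 × SE₀)/SE₁], where SE₀ uses the pooled proportion and SE₁ the separate ones.

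Worked case, cut midway between the arm means: p₁ = Φ(−0.183) = 0.4275 and p₂ = 0.5725, a difference of 0.1450. SE₀ = √(2 × 0.5 × 0.5/125) = 0.0632. SE₁ = √(2 × 0.4275 × 0.5725/125) = 0.0626. Power = Φ[(0.1450 − 0.1240)/0.0626] = Φ(0.336) = 63.1%.

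| Assumed cut-off | Proportion above cut, control vs intervention | Chi-square power, 125 per arm | n per arm for 80% |
|---|---|---|---|
| Midway between arms | 42.8% vs 57.2% | 63% | 186 |
| Control-arm median | 50.0% vs 64.3% | 63% | 188 |
| 30% control rate | 30.0% vs 43.7% | 61% | 194 |
| 20% control rate | 20.0% vs 31.7% | 56% | 219 |
| 10% control rate | 10.0% vs 18.0% | 44% | 296 |

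Fisher's exact test at the midway cut has 58% power.

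**Step 3: the non-inferiority test.** Farrington-Manning needs two proportions and a margin. The only margin the article gives for a proportion is the 5% for toxicity. No calculation can be made for the EQ-5D-5L from what is stated.

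**The case against.** The best defence is that the quality-of-life paragraph begins with a test of difference and only then adds non-inferiority. A chi-square test on a properly defined responder endpoint can answer a question about improvement, and the full protocol or the analysis plan, neither of which is shown, may define such an endpoint and a margin. All of this is fair, and it limits the point in four ways.

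- A reader might infer that showing Arm B to be no worse would take the place of showing it to be better. The text does not support that: the difference test is kept.
- A reader might infer that a non-inferiority result could end the A/B randomization. The interim rule acts on a significant result and chooses the superior arm, which points to the difference test.
- A reader might infer that the cut-off would be picked after seeing the data. The article states no cut-off, but one could be fixed beforehand in a document not shown.
- A reader might take 63% as the power of the planned analysis. It is the best of the cut-offs tried under an assumed model; the plan itself commits to no cut-off.

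The contradiction itself remains. This is not detail left to an analysis plan: the article names specific tests that conflict with its own objective, its own description of the comparison and its own sample-size basis. An analysis plan that followed the sample-size section would depart from the analysis section, and the reverse.

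**Conclusion.** The quality-of-life analysis is wrong as written: tests for proportions and a non-inferiority test are attached to a superiority question on a numeric score. On the article's own effect and SD, a comparison of means with 125 per arm has about 82% power, which supports the stated 80%. The named chi-square test would have at most about 63%, some 17 points short, and less with an off-centre cut-off. The first figure assumes a two-sided alpha of 0.05; the second also assumes normal scores, equal SD and a cut-off.

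It would be too strong to say that the second randomization is under-sized or that its question cannot be answered. The size is adequate for the comparison it was based on, and only the non-inferiority test is incapable, whatever its result, of showing improvement. Nor does the conclusion depend on any gain from baseline adjustment. Such a gain would depend on whether 15.6 is the SD of the follow-up score or of change, and on a baseline EQ-5D-5L, which the Background's reference to change implies but the article does not spell out.

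**What to change.** Replace the second paragraph of Primary endpoints with a two-sided superiority comparison (alpha 0.05) of the EQ-5D-5L score between Arms A and B at a pre-stated time point. Adjustment for baseline EQ-5D-5L, where collected, and for sex, the stratification factor of this randomization, is preferable. It is not needed to remove the contradiction, because an unadjusted comparison of means already meets the stated power. Delete chi-square, Fisher's exact and Farrington-Manning for this endpoint, and state that the interim decision on Arms A and B uses the same superiority comparison.

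The cost is a wording change to one paragraph, with a matching reference in the interim section. The sample size stays at 125 per arm. The unadjusted comparison needs no data beyond the EQ-5D-5L questionnaires already scheduled; if baseline adjustment is chosen, confirm that a baseline questionnaire is collected.

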### Survival and secondary endpoints

PFS and OS will be calculated using the Kaplan-Meier method with differences compared using the stratified log-rank test. Pre-planned subgroup analysis will occur based on the stratification factors, and also based on the use of immunotherapy vs. non-immunotherapy systemic agents. A multivariable Cox proportional hazards regression analysis will be used to determine baseline factors predictive of survival endpoints. For the endpoint of time to new metastases, a Fine and Gray competing risk analysis will be used to account for competing risk of death from any cause.

LCR will be calculated using the cumulative incidence function including mortality as competing risk.

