### Sample size calculation

#### 1^st^ randomization

The sample size is based on toxicity of SABR (grade 3-5 AEs possibly, probably, or definitely related to SABR collected by HCP). The previously published SABR-5 protocol pre-defined a 10% rate of grade ≥ 4 AEs as acceptable, and we will conservatively set a 10% grade ≥ 3 AE rate as acceptable for this study [8]. The standard and intervention arms will be accrued 1:1. Sample sizes of 299 in Arm 1 and 299 in Arm 2 are required to achieve 80% power to detect a non-inferiority margin difference of 5%, with the reference group grade ≥ 3 AEs set at 5% based on the results of SABR-5. Based on our clinical judgement, the treatment group is assumed to be 10% under the null hypothesis of inferiority and coincides with our pre-defined < 10% grade ≥ 3 AE rate. The power was computed for the case when the actual treatment group proportion is 5%. This was based on a one-sided z test (unpooled) and alpha of 0.025.

In addition, given the importance of efficacy as a secondary outcome, we wanted to ensure that this sample size would have sufficient power to rule out large effect size differences in LCR. Based on our SABR-5 trial data, the estimated LCR at 1 year is 90%. With 584 patients, assumed to be accrued over five years with an additional five years of follow-up, then we would achieve > 80% difference to rule out a non-inferiority hazard ratio margin of 1.32 (which is equivalent to SF arm having a 1-year LCR of 87%). Hence, this sample size is sufficient to provide evidence of non-inferiority for efficacy.

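### Non-inferiority is the stated objective for LCR, PFS and OS, but the planned analyses cannot establish it: PFS and OS have no margin, and the LCR margin is never carried into a comparison

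*Protocol article*

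**What the plan says.** - **Objective.** The opening paragraph of Methods says the trial is "to assess if there is non-inferiority in terms of HCP-reported grade 3 or higher toxicities, lesional control rate (LCR), PFS, cost-effectiveness, and OS".
- **PFS and OS analysis.** Under Survival and secondary endpoints: "PFS and OS will be calculated using the Kaplan-Meier method with differences compared using the stratified log-rank test". No margin for either endpoint appears in the article.
- **LCR margin.** Under Sample size calculation, 1st randomization, the margin is a hazard ratio of 1.32, equated to a 1-year LCR of 87% with single fraction (SF) against 90% with multiple fractions (MF). The setting is "With 584 patients, assumed to be accrued over five years with an additional five years of follow-up", with power put above 80%. The paragraph ends: "Hence, this sample size is sufficient to provide evidence of non-inferiority for efficacy". No alpha is given for LCR.
- **LCR analysis.** Under Survival and secondary endpoints: "LCR will be calculated using the cumulative incidence function including mortality as competing risk". No between-arm comparison follows.
- **Contrast with toxicity.** Under Primary endpoints, toxicity has both a test of difference (chi-square or Fisher) and a separate non-inferiority test (Farrington-Manning), with a 5-point margin.
- **Status.** OS is labelled exploratory. PFS and LCR are secondary endpoints without that label.

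**The concern.** A non-inferiority claim needs a margin and a rule that sets a confidence limit or test statistic against it. A log-rank test of difference supplies neither. Failing to reject equality may mean that the arms are alike, or only that there were too few events. For LCR the margin exists, but the analysis text does not use it. The margin is a hazard ratio, while the planned output is a cumulative incidence with death as a competing event. The article does not say whether the hazard ratio is cause-specific or subdistribution.

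The Discussion links a less resource-intensive recommendation to SF not being inferior for comprehensive treatment of oligometastases. If efficacy is to support that recommendation, the rule should be fixed before results are known, because a margin or confidence-limit rule chosen afterwards carries little weight.

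**Working it through.** **1. The complete case: toxicity.** Inputs from the sample size section: 5% in both arms, margin 5 points, one-sided alpha 0.025, power 80%.

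n per arm = (1.960 + 0.842)² × 2 × 0.05 × 0.95 / 0.05² ≈ 7.849 × 0.095 / 0.0025 ≈ 298.3, rounded up to 299. This reproduces the stated figure. Margin, test and sample size fit together.

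**2. LCR margin.** Under constant hazards, HR = ln(0.87) / ln(0.90) = 1.322, which matches the stated 1.32. The margin is coherent as a hazard ratio.

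**3. Why the missing LCR alpha matters.** Assume constant hazards, uniform accrual over 5 years, 5 more years of follow-up, no competing deaths, and the MF hazard λ = −ln(0.90) = 0.1054 in both arms.

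- Proportion failing = 1 − [exp(−5λ) − exp(−10λ)] / (5λ) = 0.541. Events = 584 × 0.541 ≈ 316.
- Power = Φ(ln 1.32 × √316 / 2 − z) = Φ(2.468 − z): 69.4% at one-sided 0.025 and 79.5% at one-sided 0.05.
- With events averaged over the MF hazard and a hazard 1.32 times as high (345 events): 73.2% and 82.5%.
- 80% power needs 408 events at one-sided 0.025, or 321 at 0.05.
- The final analysis is expected 3 years after last enrolment. The same calculation then gives about 253 events, with power 59.8% and 71.3%. Competing deaths lower all these figures.

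So the claim of more than 80% is reached only near one-sided 0.05.

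**4. Side by side.**

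| Endpoint | Named under non-inferiority | Margin | Rule against the margin |
|---|---|---|---|
| Toxicity | yes | 5 points | Farrington-Manning |
| LCR | yes | HR 1.32 | none |
| PFS | yes | none | none (log-rank for difference) |
| OS (exploratory) | yes | none | none (log-rank for difference) |

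**5. What a non-significant log-rank test leaves open (illustration).** The article gives no margin or event count for PFS or OS. I borrow 1.32 as an assumption and vary the number of events D, with standard error of the log HR = 2/√D.

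P(non-significant at true HR 1.32) = 1 − Φ(ln 1.32 × √D / 2 − 1.96), the opposite tail being negligible.

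| D | P(non-significant) | Largest observed HR still non-significant | Its upper 95% limit |
|---|---|---|---|
| 100 | 72% | 1.48 | 2.19 |
| 200 | 50% | 1.32 | 1.74 |
| 300 | 33% | 1.25 | 1.57 |
| 400 | 21% | 1.22 | 1.48 |

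A non-inferiority test at one-sided 0.025 would pass 2.5% of trials at that true hazard ratio, whatever D is.

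**The case against.** **The article never says that non-significance will be taken as non-inferiority.** This is correct. A reader might infer it from the mismatch, but no decision rule of that kind is written, and the toxicity text shows that the authors separate the two kinds of test. The percentages above show what such a reading would cost. They are not error rates of the plan.

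**LCR has a non-inferiority framework.** It has a margin and a power statement, so it would be wrong to say that LCR was left without one. Cumulative incidence is also a sound description when death competes, and the choice of hazard model could be left to an analysis plan. What remains is narrower: the section that fixes the LCR analysis names no comparison with 1.32. The log-rank percentages should not be applied to LCR, because the plan has no log-rank test for it.

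**The weight on OS is low.** OS is exploratory, and the Abstract confines the primary non-inferiority objective to toxicity. Both points lessen the matter for OS but do not help PFS. A reader might also judge OS precision from 100 deaths, which gives a 95% interval of 0.68 to 1.48 around an observed hazard ratio of 1.0. That count is an interim trigger. If median OS were 4 years (an assumption), 598 patients would give about 360 deaths by the final analysis and an interval of about 0.81 to 1.23.

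**This is a condensed article and the analysis plan is not shown.** That would answer a complaint about missing detail. It does not answer an objective and an analysis, both stated here, that do not match.

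**Conclusion.** The point holds as an internal mismatch. For PFS and OS, the stated objective is non-inferiority, the stated analysis tests difference and no margin exists, so the plan as written cannot establish non-inferiority for either. For LCR, the margin of 1.32 and the claim built on it are not connected to any planned comparison, and the alpha is unstated. This rests on the text alone.

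The size of the PFS and OS problem can only be illustrated, because 1.32 is borrowed and the event counts are assumed: 50% non-significant at 200 events and 33% at 300, against 2.5% false passes. The LCR power figures assume constant hazards and no competing deaths. The toxicity comparison is unaffected. The change should be made before efficacy results are known, but it does not threaten the primary conclusion.

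**What to change.** 1. **LCR (Survival and secondary endpoints).** Add a stratified hazard ratio for SF against MF with its confidence interval, for example cause-specific with deaths censored, and state which type the 1.32 margin refers to. Claim non-inferiority only if the upper limit is below 1.32 at a stated alpha. Keep the cumulative incidence as description. Restate the LCR power at the chosen alpha and at the actual time of analysis.
2. **PFS and OS (opening of Methods).** Remove non-inferiority for these endpoints. Report the stratified hazard ratio with its 95% confidence interval as estimation, and state that a non-significant log-rank test is not evidence of non-inferiority. If the team wants to keep the claim for PFS, it needs a justified margin and a confidence-limit rule.

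The cost is wording, plus fewer efficacy claims: none of non-inferiority for PFS or OS, and for LCR a claim whose power at one-sided 0.025 is below the stated 80% on the assumptions above. No change to sample size or data collection is needed for the toxicity objective.

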### Cost Utility Analysis (CUA)

A CUA will be conducted in line with the Canadian Agency for Drugs and Technologies in Health (CADTH) Guidelines for the Economic Evaluation of Health Technologies [24, 25]. Non-parametric bootstrapping will be used to estimate the 95% confidence intervals (CIs) and to construct a cost-effectiveness acceptability curve. Sensitivity analysis will be conducted by varying the major drivers of costs. All costs will be adjusted to a base year using the healthcare component of the Statistics Canada Consumer Price Index [26] to adjust for price inflation over time. Subsequent incremental cost per unit of OS improvement using OS outcomes will be explored. Although Canada has a single-payer health insurance system, the provincial and territorial governments are responsible for health care administration and delivery. Our analyses will be undertaken from the perspectives of the British Columbia and Ontario provincial Ministries of Health as we expect these provinces to accrue the highest number of patients. We will gain consent from all trial participants to prospectively assess their patient-level records pertaining to the frequency of hospital admissions and the use of targeted- and immuno-therapies. We will use the resource costing method whereby utilization data are collected from existing data sources and then multiplied by unit costs.

